### Randomization and blinding

Prior to the delivery of the first scale-up strategy, schools within each LHD will be randomly allocated to either the intervention or control condition using a computerized random number function in a 1:1 (intervention: control) ratio. Randomization will be stratified by school size and social socio-economic location, as determined by Socio-Economic Indexes for Areas categorization using school postcodes, (33) given the socio-economic association with implementation of school nutrition programs (34). Randomization will be completed by a statistician not otherwise involved in the trial. Due to the nature of the intervention, participants will not be blinded to group allocation. However, research staff assessing the outcomes at follow-up will be blinded.

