### Implementation strategies

A series of implementation strategies were developed with the aim of maximizing school adoption of the SWAP IT program in eligible schools that have not yet adopted the program. These implementation strategies were developed for each of the LHDs independently, based on their existing capacities and local contexts. Implementation strategies for each participating LHD (‘site’) were co-designed by LHD health promotion staff and other stakeholders, with support provided by National Centre of Implementation Science (NCOIS) implementation scientists and SWAP IT developers from the University of Newcastle. The development process included: (i) planning workshops facilitated by University staff that drew on tacit knowledge and experience of health promotion staff who had considerable experience working with schools; (ii) evidence regarding barriers to school adoption and implementation of SWAP IT collected by the research team as part of previous SWAP IT trials, (iii) data from systematic reviews and pilot trials regarding the effectiveness of strategies to facilitate adoption (32). During the workshops, theoretical framework tools were used to facilitate the selection of strategies to address barriers that were aligned to individual LHD capacity and contexts (35–37). Processes may have also been undertaken by LHDs to identify strategies to support access and engagement of priority populations within their region to ensure school adoption and implementation of SWAP IT does not further exacerbate health inequities. This may have included consultation and engagement processes with Aboriginal, or Culturally and Linguistically Diverse individuals, groups or stakeholders.

Across the 10 participating LHDs, six broad implementation strategies to maximize school adoption of SWAP IT emerged. The combination of these six strategies employed by each LHD will differ and will be executed over a period of 6 months. Once a school adopts SWAP IT, they will not receive any subsequent implementation strategies, and will select which school term they would prefer to receive the program. The SWAP IT messages are delivered weekly to parents and carers via usual school-parent communication channels for one school term (one message per week), followed by two messages per term on an ongoing basis. A school must adopt SWAP IT in order to receive the program.

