We will employ component IPD component network meta-analysis to compare and rank the effects from all the tested strategies on the primary trial outcome (40). For this analysis we will also include the three randomized controlled trials from the pilot, (26) expanding the network and providing pooled individual level data from 13 randomized controlled trials. We will explore combining ‘educational meetings and educational materials’ into a single component for analysis given their shared underlying behavioral targets. We will adjust for prognostic factors and exploration of strategy—covariate interactions to identify if and to what extent effects vary by participant, population or other contextual factors (effect modifier) (40). We will also employ component network meta-analyses to model additive main effects (separate effects for each element or component of an implementation strategy); two way interactions (synergistic/antagonistic effects of components), and full interactions (different effects from each combination of components). The analyses will be performed under a Bayesian framework. There are no established methods for sample size calculations for component network meta-analysis.

For the secondary outcomes assessed via an online or telephone survey, data screening strategies were employed during survey development to minimize incomplete or inaccurate responses. These strategies included the use of mandatory fields (i.e., participants were unable to leave a survey item blank, but could select ‘prefer not to say’), minimizing the inclusion of open responses and reducing the survey length. Best practice recommendations for data screening will also be employed following data collection, including visually inspecting data to identify data entry errors or implausible values for each variable, and calculating distributional characteristics of items to assist in identifying outliers or extreme values (41).

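### Two-way interaction models for six components are planned without any limit on terms, but 13 trials supply at most 13 randomised contrasts if the pilot trials are two-arm

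*Protocol article*

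**What the plan says.** The Implementation strategies section of the protocol article reports that "six broad implementation strategies to maximize school adoption of SWAP IT emerged". Each district uses its own combination. The Abstract adds that six of the ten districts chose an active comparator holding at least one strategy.

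Under Randomization and blinding, "schools within each LHD will be randomly allocated to either the intervention or control condition", "in a 1:1 (intervention: control) ratio". Each new trial therefore has two arms.

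Sample size and data analysis plans an individual-data component network meta-analysis to "compare and rank the effects from all the tested strategies on the primary trial outcome". On the network it says that "we will also include the three randomized controlled trials from the pilot", "providing pooled individual level data from 13 randomized controlled trials". It will explore merging educational meetings and educational materials "into a single component for analysis given their shared underlying behavioral targets". The models named are additive main effects, "two way interactions (synergistic/antagonistic effects of components), and full interactions (different effects from each combination of components", all under a Bayesian framework. The section remarks that no established sample size method exists for such an analysis. It gives no condition of estimability for the interaction terms.

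Under Objectives, this work serves secondary objective 1, which is worded as exploration. The primary analysis is a logistic regression within each trial.

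**The concern.** A two-arm trial gives one randomised contrast between two packages of components. If one arm receives A, B and C and the other receives nothing, the trial informs only the sum A + B + C + AB + AC + BC. If the comparator is A and the intervention is A with B, it informs only B + AB. Separating an interaction from its main effects needs several trials whose packages differ in the right way. A model with more parameters than independent contrasts cannot be separated fully, whatever the number of schools.

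A Bayesian fit with proper priors does not fail in that situation. It returns an interval for every term. Where the likelihood is flat, the interval reflects the prior and whatever the prior ties to the identified terms. Statements about synergy or antagonism between strategies could then be read by health districts as trial evidence when no randomised comparison supports them.

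**Working it through.** The article gives no parameter count or sample size for the component analysis, so there is no stated figure to reproduce on this point. Its one sample size figure, about 30 schools per group for 10% against 40% adoption, belongs to the single trials and is not in dispute. The pooled-variance formula gives 32 and the arcsine formula 29.8.

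**Inputs**
- Components: c = 6 (Implementation strategies), or c = 5 after the possible merge (Sample size and data analysis).
- Trials: 10 new and 3 pilot, 13 in all.
- Arms: 2 in each new trial (Randomization and blinding). The article does not give the pilot arms; 2 is assumed, and 3 and 4 are shown as a range.
- Component effects are taken to be estimated within trials, with a separate baseline for each trial.

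**Parameters**
- Additive model: c, so 6 or 5.
- Additive plus all pairs: c + c(c − 1)/2, so 6 + 15 = 21 or 5 + 10 = 15.
- Full interaction over observed combinations: distinct arms minus one in a connected network. With 13 two-arm trials this cannot exceed 13.

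**Contrasts: sum of (arms − 1) over trials**

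| Pilot arms per trial (assumed) | Contrasts | Shortfall, 21 parameters | Shortfall, 15 parameters |
|---|---|---|---|
| 2 | 10 + 3 × 1 = 13 | 8 | 2 |
| 3 | 10 + 3 × 2 = 16 | 5 | none by count |
| 4 | 10 + 3 × 3 = 19 | 2 | none by count |

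The rank of the contrast matrix cannot exceed the number of contrasts, so each shortfall is a minimum. Between-trial heterogeneity would need further information.

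**Would dropping pairs never delivered together be enough?** With 13 contrasts, six main effects leave room for at most 13 − 6 = 7 pairs. One package of five components already contains 10 pairs (6 + 10 = 16), and a package of all six contains 15. With five components there is room for 13 − 5 = 8 pairs, and one package holding all five contains 10. Omitting unobserved pairs therefore need not bring the model within the rank.

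**Illustration under assumed layouts.** The cell entries of Table 1 are not readable in the text at hand, so random layouts stood in for them: 3,000 for each coding, 13 two-arm trials, at least two components per intervention, and a single-strategy comparator in six trials. On average about 0.5 of 15 pairwise terms were individually estimable (1.4 of 10 with five components). The additive model had full rank in about 99% of layouts. The network was connected in 5% of layouts with six components and 14% with five. These figures show what can happen. They do not describe the actual design.

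**Precision where a term is identified.** At 10% against 40% with n schools per group, SE(log OR) = √[1/(0.1n) + 1/(0.9n) + 1/(0.4n) + 1/(0.6n)]. This is 0.71 for n = 30 and 0.50 for n = 60. A difference of two such contrasts has SE √2 times as large, 1.01 or 0.71, against a design log odds ratio of 1.79. Even an identified interaction that rests on two contrasts would be imprecise.

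The article also says that audit and feedback reaches schools through educational materials, local facilitation and opinion leaders. That component may therefore be nearly collinear with others, which would lower the usable rank further.

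**The case against.** The strongest reply is that the article never promises every pair. It names two-way interactions as a class, and an analyst would leave out pairs that were never delivered together. That is fair, and 21 and 15 are upper counts for a model that the text does not spell out. But the text sets no limit, and the working shows that leaving out unobserved pairs may not be enough.

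Three stronger readings are tempting, and the documents do not support them.
- A reader might infer that the full-interaction model needs one parameter for each of the 2^6 − 1 = 63 possible combinations. The article defines it by combination of components. Over the combinations actually delivered it is an ordinary network meta-analysis, identified within each connected part.
- A reader might infer that all the rankings come from the prior. Rankings of additive effects, or of observed combinations in a connected network, can rest on data.
- A reader might infer that the network is disconnected. That cannot be judged without the Table 1 entries. The strategies were co-designed rather than drawn at random, active comparators may hold more than one strategy, and districts without an active comparator would appear to share a no-support control.

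Two further points stand. The two-arm form is documented only for the new trials. Priors and model-selection rules may be in an analysis plan that is not shown, so their absence is not counted here. A plan of that kind can narrow the list of interactions but cannot create contrasts. The remark that no sample size method exists does not meet the point either, since counting parameters against contrasts needs none.

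**Conclusion.** The concern holds in limited form. An unrestricted two-way model exceeds what the network can identify by at least 8 parameters with six components and at least 2 with five, if the pilot trials are two-arm. With six components it still fails at 16 or 19 contrasts. With five, the count alone no longer excludes it at 16 or more, though the actual rank could still be too low. Interactions outside the identified space, and ranks built on them, would follow the prior.

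The counts rest on within-trial estimation and on the assumed pilot arms. They do not depend on the entries of Table 1, which can only lower the rank. Additive main effects and observed combinations within a connected network are outside this criticism. The consequence is confined to exploratory secondary objective 1; the per-trial logistic regressions and the primary objective are untouched. It is worth correcting because it decides what the trial can say about synergy between strategies, but it does not threaten the main result.

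**What to change.** 1. Name the additive main-effects model as the main component analysis.
2. Before outcome data are pooled, build the contrast matrix from Table 1 and the pilot arms, and report its rank under both the merged and the unmerged coding of meetings and materials.
3. Fit only a short list of two-way terms, named in advance, that this matrix identifies.
4. Keep the full-interaction model, restricted to observed combinations within connected parts of the network.
5. Rank only estimable effects, and label any other output as prior-driven.

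The cost is one rank check, some wording in the protocol or analysis plan, and fewer interaction claims. No change to data collection or to the trials is needed.

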### Trial governance

The trial will be overseen by a Steering Group, comprised of representatives from each LHD, including: Aboriginal Health Promotion Managers; program developers, implementation scientists, trialists and research dietitians from the University of Newcastle. Roles and responsibilities will be documented in a Terms of Reference for the Group. LHDs will be responsible for the selection of implementation strategies for their jurisdiction, and execution of some of the strategies to schools. The University of Newcastle will be responsible for facilitating trial workshops, ethics, data collection, monitoring and quality assurance, data management and analysis. A Community of Practice, established in the pilot, (26) will also be employed to support the interpretation of trial results and pooled analyses, exchange tacit knowledge and experience and identify opportunities for improvement.

## Discussion

This protocol provides a comprehensive description of a novel research design, employing individual level participant (i.e., ‘school’) data component meta-analysis, to help generate evidence that can better inform approaches to support the adoption and implementation of health promotion interventions at scale. The study will provide rigorous evidence of the effects of a variety of implementation strategies, employed in different contexts on the adoption of the SWAP IT school lunchbox program.

Evidence generated from this research will help address an important constraint of the current literature, with systematic review evidence identifying few rigorous trials that have tested strategies to implement health promotion interventions at scale. The strategies tested within this study have been developed following a systematic co-design approach with implementation researchers, LHD health promotion staff and other stakeholders. In addition to considering the evidence-base (i.e., barriers and enablers to adoption of school-based programs, and the effectiveness of implementation strategies), this process included working with LHD health promotion staff to consider the human, technical and financial resources available in LHDs responsible for strategy delivery. Applying this type of systematic approach to scale up has been recommended by implementation and scale-up experts to help address a common pitfall of scale-up research, which is the diminishment in effect of interventions with proven efficacy when delivered at scale (42, 43).

The currently limited evidence base has resulted in a failure to provide guidance on the crucial issue of context, with strategies that effectively improve implementation in one context potentially ineffective or inappropriate to deliver in another (22). Through partnering with 13 NSW LHDs (including three from the pilot) to conduct this research, schools from all sectors and located within the majority (86%) of the state of NSW will be represented. These LHDs encompass socioeconomically and geographically diverse regions, ensuring the contexts in which these strategies are tested are diverse and representative of the broader setting (31). In order to further address the issue of context, future research should potentially consider identifying and addressing other contextual, sectoral and political factors that may be influential in maximizing school adoption of the SWAP IT program. For example, the World Health Organization’s Health Promoting Schools Framework recommends employing a comprehensive approach, encompassing education (e.g., learning and curriculum), environmental (e.g., culture and policies) and partnership (e.g., families, health professionals and educators, teachers and community) components, to enhance the effectiveness of health promotion programs (44). Employing individual-level participant data component meta-analysis within this research provides an opportunity to gather robust evidence on the types of strategies that are effective in improving implementation of SWAP IT, and in what context. Additionally, it addresses a noticeable constraint in the current literature, that is, the substantial heterogeneity in trial design and measures employed in the few studies that have tested strategies to implement health promotion programs at scale. IPD meta-analysis is considered the gold standard for combining data from randomized trials and has several advantages over other analytical approaches (45–47). These advantages include the increase in statistical power compared to aggregate data meta-analysis, the ability to standardize the analysis across studies to ensure consistency in outcome measures, and enhancing the ability to effectively explore heterogeneity in participant characteristics (i.e., schools and LHDs) and treatment effects (i.e., implementation strategies) (45–47). This type of analysis has been frequently employed to synthesize the effects of health behavior interventions (48–50). For example, the Transforming Obesity Prevention for CHILDren (TOPCHILD) Collaboration uses IPD meta-analysis to assess the effectiveness of obesity-prevention interventions on child weight outcomes, and also assess differential effects by individual- and trial-level characteristics (50).

## Ethics statement

The studies involving humans were approved by Hunter New England (2019/ETH12353); University of Newcastle (09/07/26/4.04); NSW of Department of Education (2018247); and the Maitland-Newcastle, Sydney, Wollongong, Bathurst, Parramatta, Wagga Wagga and Canberra-Goulburn Catholic Dioceses. The studies were conducted in accordance with the local legislation and institutional requirements. The participants provided their written informed consent to participate in this study.
